## Abstract

**Introduction:**

With the growing older adult population, the European Union emphasizes the need to promote research in healthy aging trough multidisciplinary and innovative approaches, including the integration of advanced technologies like virtual reality (VR) in cognitive rehabilitation. This reflects the increasing awareness of the importance of addressing challenges related to neurodegenerative diseases in the older adult population. Our study aims to present a protocol that will assess the feasibility and provide a preliminary measure of effectiveness for an intervention using immersive CR technology for cognitive remediation (CR) in individuals with Mild Cognitive Impairment (MCI).

**Methods:**

A feasibility randomized controlled clinical study will involve 30 individuals who are over 65 years old, both sex, who meet the diagnostic criteria for MCI from the University Hospital of Cagliari, randomly assigned to either the experimental condition or control group. Both groups will continue to receive standard pharmacological therapy. The experimental group will undergo a 3-months cognitive remediation program using fully immersive VR with two sessions per week. Each session will last a maximum of 60 min and will be supervised by expert health professionals. In contrast, the control group will continue with standard care. The intervention program will be carried out by s psychiatric rehabilitation technicians and speech therapists, emphasizing a comprehensive framework aligned with healthcare needs. Feasibility will be assessed based on tolerability, including dropout rates and acceptability, which considers the proportion of recruited participants among those considered eligible and on side effects and level of satisfaction. The preliminary measures of effectiveness will be evaluated on quality of life, cognitive functions, biological and social rhythms, depressive symptoms and anxiety.

**Results:**

The trial findings will be submitted for publication in international peer-reviewed journals and shared at international meetings and conferences.

**Discussion:**

This study aiming to assess the feasibility and preliminary effectiveness of a fully immersive VR/CR program for MCI in order to give data for a subsequent confirmatory trial. The results of the pilot RCT are expected to significantly contribute to research on the prevention of neurocognitive degeneration, with a specific emphasis on enhancing the application of technologies. The strengths of this work are the high technological innovation program for mental health treatments for *healthy aging* and multidisciplinary approach emphasizing a holistic framework aligned with health needs.

## Introduction

1

As the global population continues to age, mild cognitive impairment (MCI) and dementia have become primary contributors to disability, particularly among the older adult population (1, 2). MCI delineates a transitional stage between the typical cognitive decline (CD) attributed to progressive aging and the initial phase of dementia (3, 4). Italy is the European country with the oldest population (23%), projections indicate that by the year 2050, one out of every five individuals in Italy will be in old age. This leads to a reduction in the working-age population and an increase in direct and indirect healthcare/social costs associated with the rising health problems (5). Risk factors such as physical, cognitive, and social inactivity are estimated to be responsible for about 40% of the risk of developing dementia over the lifespan (6). In general, approximately 50% of people with MCI progress to dementia within 3 years (7). Furthermore, CD is associated with depressive and anxiety symptoms and they both contribute to functional deterioration in daily tasks (7, 8). These conditions reduce the quality of life and the regulation of biological and social rhythms (9–11). Among others risk factors hypertension and cardiometabolic play a crucial role in the onset of cognitive dysfunction and progression to clinical over dementia (12). However, the pharmacological treatment and management of these conditions in older subjects is complex (13, 14) and may often result in worsening of cognitive progression (15). Growing attention has been given from researchers and from the European Union (EU) in recognizes the important goal of promoting research in the field of healthy aging, particularly non-pharmacological interventions aimed at preventing and/or delaying CD (16, 17).

Recent literature reviews have highlighted promising outcomes regarding cognitive training or cognitive remediation (CR) interventions and physical activity in improving cognitive performance in older adult individuals in an integrated public health approach, irrespective of CD (2, 18–21). Moreover, a substantial amount of evidence in the field of neuropsychological disorders, encompassing conditions such as dementia and MCI, has been documented (2, 22, 23). Cognitive training or cognitive remediation programs fall under the broader category of cognitive rehabilitation and utilize various cognitive-behavioral techniques. These treatments share key components, such as the identification of personal goals, the development of strategies to achieve them, and the application of these strategies to everyday life (20). Consequently, interventions should utilize behavioral techniques that effectively facilitate rehabilitation outcomes. Scientific evidence suggests that cognitive remediation interventions yield positive results in the treatment of MCI, both in terms of cognitive outcomes and overall functioning (2, 24). CR interventions are defined as behaviorally based interventions aimed at improving cognitive processes (memory, attention, executive functions, social cognition, and metacognition) with the goal of achieving persistence of results and their generalization (25–27).

The need to promote research in healthy aging trough multidisciplinary and innovative approaches, including the integration of advanced technologies like virtual reality (VR), in cognitive rehabilitation has also been emphasized by the EU (16, 17). This reflects the increasing awareness of the importance of addressing challenges related to neurodegenerative diseases in the older adult population. The use of VR as a CR tool has shown several scientific advancements in recent years (28–30). VR serves as a crucial tool facilitating the learning and/or enhancement of various skills, owing to its ability to make learning experiences more realistic and ecologically valid compared to traditional intervention techniques (31). Recent systematic reviews suggest that the utilization of innovative technologies, such as immersive VR, in the treatment of CD in MCI, may lead to positive outcomes (29, 32). These findings not only indicate improvements in cognitive functions (memory, language and executive function) but also achieve an overall clinical, personal and social functioning enhancement (33). Although there is positive evidence, the methodological quality still requires improvement. Frequently, studies lack detailed descriptions of the VR intervention and the methods employed during sessions. Moreover, the majority of the studies did not specify the framework for developing the intervention, which is crucial for explaining the coherence between hypotheses, outcomes, methods, and the games used in the VR program and the cognitive domains being trained (34). This lack of information hinders the establishment of a standard operating procedure, essential for the reproducibility of the intervention and the development of a future golden standard (29). It is therefore crucial to promote clinical trials implementing CR interventions with fully immersive VR programs. Specifically, training should target all cognitive functions aligned with the identified health needs for MCI, further promote the generalization of trained skills to everyday life (35, 36). Lastly, an approach centered on personal recovery goals and multidisciplinary is essential to address the complexity of emerging needs.

### Aims

1.1

Given all these considerations, the hypothesis of the study is that a CR intervention using fully immersive VR in the older adult population with MCI may yield positive outcomes in terms of feasibility (acceptability, tolerability and side effects) and preliminary clinical outcomes (cognitive functions, quality of life, biological rhythms, anxiety and depression symptoms). The aim of this study is to presents the research protocol of a randomized controlled trial (RCT). The RCT is designed to evaluate the feasibility and preliminary clinical efficacy of a CR program through fully immersive VR for treating CD in MCI among individuals over 65 years of age.

## Materials and methods

2

### Study design

2.1

This study is a feasibility randomized controlled (two-arm) clinical study protocol, adhering to the CONSORT flow diagram extension for feasibility study (37). The protocol is written according to the SPIRIT Standard Protocol Items (38). The RCT will involve individuals aged 65 and above with MCI. The experimental group will participate in a three-month CR program utilizing fully immersive VR, consisting of two sessions per week in addition to standard care. In contrast, the control group will receive only standard care. Consistent with the study outcomes (primary outcome of feasibility and secondary outcome of preliminary efficacy measurement), a randomized controlled design is essential even at the feasibility stage to ensure greater scientific rigor. For both outcomes, the variables will be assessed through comparison between the two groups.

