### Randomization

2.3

Participants meeting the eligibility criteria will be randomly assigned to two groups (intervention and control group). A computer-generated randomization list will be used for the random allocation sequence, carried out at the University of Cagliari. A standard single blinding randomization procedure will be employed without stratification; however, if the sample will not be homogeneous, block stratification by age and sex, with a maximum of two blocks, will be implemented. An external statistician, not involved in the research project (thus not involved in assessments or interventions), will generate the two lists using a list generator and before it will anonymize the allocation using identification codes. The researchers involved in the assessments (initial and post-intervention) will be blinded to the participants’ group assignments.

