#### Primary outcomes

2.5.1

The primary outcome assesses the feasibility of the study, focusing on acceptability, tolerability (dropout rate), level of side effects and satisfaction. Variables in terms of acceptability, tolerability and satisfaction level will be assessed using an *ad-hoc* data sheet. Acceptability is measured as the proportion of recruited patients among those deemed eligible, while tolerability is assessed as the proportion of patients completing the trial intervention among those included.

The Italian adaptation of the Simulator Sickness Questionnaire (SSQ) will be used to record side-effects. The SSQ is a 16-item self-report questionnaire assessing the frequency of potential side effects related to the use of VR technologies, such as nausea, dizziness, headaches, eye fatigue, etc. (39).

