### Sample size considerations

2.9

In the registered clinical trial, our protocol outlined the recruitment and randomization of 30 eligible subjects in accordance with the predefined inclusion criteria.

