### Resource identification initiative

4.1

The primary objective of the trial is to comprehensively assess feasibility, particularly focusing on recruitment and retention rates. This evaluation provides essential insights for determining sample sizes in subsequent confirmatory trials. Additionally, to assess the side effect and satisfaction level of a VR-implemented CR tool, known as CEREBRUM. The secondary objective is to investigate cognitive and psychosocial variables. The hypothesis suggests that utilizing a CR with fully immersive VR program, with ecological instruments, can enhance cognitive abilities as well as other social and personal outcomes. The aim of this protocol study is to report the protocol of the trial, underlining methodological aspects in order to provide a response to the emerging health needs in line with the new evidences.

Indeed, the implementation of VR as a rehabilitative treatment in individuals with MCI is yielding positive results. Particularly, in a recent meta-analysis involving only people with MCI, a positive effect on clinical cognitive outcomes, specifically memory, language, and global cognition, was observed (29). However, few results are available regarding the improvement of clinical and functional outcomes due to the heterogeneity of variables and tools used, and the quality of the studies still need to improve (29, 53, 54). In general, the use of technological innovation and tools such as VR, based on the evidence described, can make the rehabilitation experience more engaging and facilitate the generalization of skills to real-life contexts, as the scenarios closely resemble those encountered in everyday life (54, 55). Naturally, technology should not replace the importance of the therapeutic relationship; rather, these are valuable tools that support rehabilitative techniques, with the relationship with the therapist remaining fundamental. Therefore, as in the intervention methodology used, exposure to VR is time-limited within each session.

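### The plan assesses the primary feasibility variables by comparing the two groups, but most of them, as defined, have no control-arm value; they should be estimated instead, with completion separated from retention

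*Protocol article*

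**What the plan says.** Section 2.1 (Study design) names feasibility as the primary outcome and preliminary efficacy as the secondary outcome, then fixes one mode of analysis for the two: "For both outcomes, the variables will be assessed through comparison between the two groups".

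Section 2.5.1 (Primary outcomes) lists the feasibility components as "focusing on acceptability, tolerability (dropout rate), level of side effects and satisfaction". It defines the first as follows: "Acceptability is measured as the proportion of recruited patients among those deemed eligible". It defines tolerability as the share of the participants included who complete the trial intervention. Side effects are recorded with the Simulator Sickness Questionnaire (SSQ), which is described as covering effects of VR use.

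Sections 2.1 and 2.7 give the control arm standard care only. Section 2.8 (Data analyses) reports satisfaction with the experimental intervention descriptively. The only outcome comparison it describes is of means between groups over time. Section 4.1 restates the primary objective as assessing feasibility, "particularly focusing on recruitment and retention rates", to inform the size of later trials.

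**The concern.** The sentence in section 2.1 and the definitions in sections 2.5.1, 2.7 and 2.8 cannot all be followed. This is a conflict within the text, not a detail that a condensed article leaves out, so an unseen analysis plan would have to override one of the statements.

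Two things are at stake:

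- **Misreading.** Where a comparison can be forced, a non-significant difference between small arms could be reported as evidence that the programme is tolerable.
- **Choice after the fact.** Completion, dropout and retention are used as if they were one quantity, and the denominator could be the VR arm or all participants. If this stays open until the data are in, the more favourable version can be chosen.

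**Working it through.** **Inputs.** The total of 30 comes from section 2.9 ("our protocol outlined the recruitment and randomization of 30 eligible subjects in accordance with the predefined inclusion criteria"). No power, rate or precision target is attached to it, so there is no calculation to reproduce. Participants are "randomly assigned to two groups (intervention and control group" (section 2.3) with no stated ratio; I assume 1:1, so 15 per arm. All retention and completion rates below are assumptions, because the article gives none.

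**Step 1. Does each component have a value in both arms?**

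| Component | Definition in the article | Control-arm value? |
|---|---|---|
| Acceptability | Recruited / eligible (2.5.1) | No. Settled before allocation; eligible patients who are not recruited never enter an arm |
| Tolerability, as defined | Completed the trial intervention / included (2.5.1) | No. Controls have no trial intervention (2.1, 2.7) |
| Tolerability, as labelled | Dropout rate (2.5.1); retention (4.1) | Yes, if it means remaining under assessment from t0 to t3 (2.5) |
| Satisfaction | With the experimental intervention, descriptive (2.8) | No |
| Side effects | SSQ, VR-related symptoms (2.5.1) | Only as a background rate, if controls complete it |

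The comparison of means in section 2.8 does not fit a recruitment or completion proportion either.

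**Step 2. Are completion and retention the same?** No. A VR participant can stop the sessions and still attend t1 to t3, and a control can be retained with nothing to complete. The numerators differ. The denominator for completion may be the VR arm or all 30, and for retention it is everyone randomised.

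**Step 3. What would a between-arm retention comparison show?** With n = 15 per arm, two-sided 5%, and p̄ the mean of the two rates, the normal approximation is

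Power = Φ{[|p1 − p2| − 1.96·√(2p̄(1 − p̄)/n)] / √[(p1(1 − p1) + p2(1 − p2))/n]}

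For 70% against 90%: (0.20 − 1.96 × 0.1461)/0.1414 = −0.61, and Φ(−0.61) = 0.27. Exact Fisher power sums the binomial probabilities of all 16 × 16 outcomes with p ≤ 0.05.

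| Assumed retention | Normal approx. | Exact Fisher | n per arm for 80% power (normal approx.) |
|---|---|---|---|
| 80% v 90% | 11% | 4% | 199 |
| 70% v 90% | 27% | 15% | 62 |
| 60% v 90% | 47% | 33% | 32 |

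If all 15 controls are retained, Fisher's test reaches 5% only when the VR arm keeps 10 or fewer:

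- 10/15 v 15/15: p = 2 × C(15,10)/C(30,25) = 2 × 3003/142506 = 0.042.
- 11/15 v 15/15: p = 2 × C(15,11)/C(30,26) = 2 × 1365/27405 = 0.10.

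Losing 4 of 15 VR participants against no controls would therefore not be significant.

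**Step 4. What does estimation give?** The Clopper-Pearson limits for x of n are the 2.5% quantile of Beta(x, n − x + 1) and the 97.5% quantile of Beta(x + 1, n − x).

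- Completion in the VR arm: 12/15 = 80% (52% to 96%); 15/15 = 100% (78% to 100%).
- Retention over both arms: 24/30 = 80% (61% to 92%).
- Acceptability with 30 recruited: 30/40 = 75% (59% to 87%); 30/60 = 50% (37% to 63%).

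These intervals are wide, but each answers a question that the trial asks.

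**The case against.** The strongest defence is that the sentence in section 2.1 is a loose summary and the detail elsewhere is sound. Section 2.8 already treats satisfaction descriptively. Dropout, the label in section 2.5.1, exists in both arms, because participants are followed from t0 to t3. SSQ symptoms such as nausea or headache also occur without VR, so a control-arm background rate would be interpretable. All of this stands, and it means that not every component is impossible to compare. It does not rescue acceptability, intervention completion or satisfaction, and it does not settle whether tolerability means completion or retention.

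Three stronger readings are tempting, and the document does not support them:

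- **That the primary question cannot be answered.** Section 4.1 and the abstract's discussion state a descriptive purpose, to supply data for a later trial. The rates can all be estimated from the data to be collected.
- **That no result could count as not feasible.** The Aims hypothesise that the programme "may yield positive outcomes in terms of feasibility (acceptability, tolerability and side effects") without putting a figure on positive. This is a condensed article, however, and progression criteria may stand in the full protocol or analysis plan. Their absence here is no finding.
- **That tolerability is capped at 15/30 = 50%.** That follows only if both arms are pooled in one denominator. The article does not say so, and pooling would not fit a comparison by arm.

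**Conclusion.** The contradiction holds: section 2.1 assigns the primary variables an analysis that the article's own definitions rule out for acceptability, intervention completion and satisfaction, and that for side effects depends on giving the SSQ to controls. The ambiguity between completion and dropout or retention, with its open denominator, also holds. For retention the comparison can be made, but it has roughly 15% to 27% power for a 20-point difference (70% v 90%), so a null result would say little about tolerability.

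The power and interval figures rest on 1:1 allocation and assumed rates. The contradiction rests on neither. This should be fixed before recruitment opens. It is not fatal, because no data would be lost and the descriptive aim remains attainable.

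**What to change.** Limit the between-group sentence in section 2.1 to the secondary outcomes. State that the primary analysis is estimation, with exact 95% confidence intervals for proportions:

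- **Acceptability:** recruited / eligible, one figure for the whole trial.
- **Tolerability:** completers of the intervention / all randomised to VR.
- **Retention at t1, t2 and t3:** assessed / randomised, described by arm without a test, and named separately from tolerability in sections 2.5.1 and 4.1.
- **Satisfaction:** VR arm only.
- **SSQ:** VR arm, with controls shown only as a descriptive background rate if it is collected there.

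Cost: no extra participants or data. The trial is registered and has ethics approval (section 2.10), so the change may need an amendment or a registry update before recruitment starts. The other price is that wide intervals, such as 52% to 96% for 12 of 15, are shown openly.

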### Participants

2.2

The RCT will involve individuals diagnosed with MCI, who will be recruited from the Cardiology and Internal Medicine departments at the University Hospital of Cagliari (San Giovanni di Dio Civil Hospital). The enrollment process will be conducted at the Consultation and Psychosomatic Psychiatry Center within the same University hospital. Eligible participants must meet the following inclusion criteria: age 65 and above, a diagnosis of Minor Neurocognitive Disorder (MND) specifically MCI based on DSM-V criteria (4), of any genders, and able to provide informed consent. Exclusion criteria include failure to meet inclusion criteria, a diagnosis of epilepsy or severe visual impairments due to potential risks associated with extensive virtual reality stimulation, and severe illnesses that hinder attendance at bi-weekly interventions.

### Randomization

2.3

Participants meeting the eligibility criteria will be randomly assigned to two groups (intervention and control group). A computer-generated randomization list will be used for the random allocation sequence, carried out at the University of Cagliari. A standard single blinding randomization procedure will be employed without stratification; however, if the sample will not be homogeneous, block stratification by age and sex, with a maximum of two blocks, will be implemented. An external statistician, not involved in the research project (thus not involved in assessments or interventions), will generate the two lists using a list generator and before it will anonymize the allocation using identification codes. The researchers involved in the assessments (initial and post-intervention) will be blinded to the participants’ group assignments.

